#### Data analysis plan

Analyses will test whether participants who played the game (treatment arm) relative to control participants who have not received any encouragement to play the game:Improved knowledge about SRH care, including menstruation, menstrual hygiene, fertility awareness, and SRH/menstrual management products.Improved attitudes, confidence, and decision support for managing her self-care, SRH, negotiating consent and contraceptive use, and accessing/using DTC information, products, and care.Improved assertion of self-identity through DTC linkages to career, safety, and personal well-being resources, and improved self-efficacy.

Analysis of the quantitative study data will be conducted using STATA and SPSS where appropriate. Descriptive analysis will be performed for all variables, and unadjusted comparisons between experimental and control arms will be conducted. Descriptive statistics will be performed, including frequencies, means, and standard deviations. In addition, chi-square tests and t-tests will be used to examine associations in the data. A probability value of less than 0.05 will be considered statistically significant for all statistical tests conducted. Continuous variables will be tested for normality, and non-normal values will be categorised or transformed appropriately.

The following two analyses will be done to satisfy the objective of the study:Univariate descriptive analysis such as frequency, percentages, the mean, and standard deviation will be computed for different background characteristics and knowledge, attitude, and practice (KAP) variables.KAP variables will be analyzed using Z-test/t-test for encouragement and control arms in two points from the same respondent.The net change in KAP and its significance will be calculated using difference-in-difference (DID) analysis. The DID analysis will be done using the following formula. (See Table 5)

**Table 5 Tab5:** Difference-in-difference analysis pathway in RCT

	Experimental arm (s = 2)	Control arm (s = 1)	Difference (s)
Baseline (t = 1)	Y_12_	Y_11_	Y_21_ –Y_11_
Follow-up (t = 2)	Y_22_	Y_21_	Y_22_ –Y_12_
Difference (t)	Y_22_ –Y_21_	Y_12_ –Y_11_	Net change (DID) = (Y_22_ – Y_21_) – Y_12_ – Y_11_

The level of significance of DID will be tested using the below equation through regression analysis.$${\text{Y }} = {\text{ a }} + {\text{ b}}_{{{\text{1s}}}} + {\text{ b}}_{{{\text{2t}}}} + {\text{ b}}_{{{\text{3s}}*}}$$

where.

Y = dependent/response variable.

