a = constant.

s and t are study arm and time, respectively.

b_1_ and b_2_ are slopes for the study arm and time, respectively.

b_3_ = treatment effect.

s*t is a dummy variable indicating treatment status.

The significance level of the test will be measured using a p-value < 0.05 (95% level of significance as per the sample size estimation).

The primary comparison of the binary outcomes between intervention groups at baseline and follow-up will use mixed-effects longitudinal logistic regression, with random effects for the individual over time. The baseline will be included as a time point only. A categorical time effect will be used (profile model). A “difference-in-differences” analysis will compare the treatment arms. Statistically, this amounts to testing for an interaction between time and treatment arm in the longitudinal model. Since the treatment assignment is at random, this “unadjusted” analysis will provide a causal effect of the intervention. However, we will also conduct secondary analyses, adjusting for potentially relevant covariates (e.g., age, education, etc.), in addition to time and treatment arm, using backward model selection at the α = 0.15 threshold level. These secondary analyses may improve the precision (power) of estimating the treatment effect and reduce any bias due to random imbalances between arms.

The primary analyses will use an intent-to-treat approach and analyze all subjects according to a randomized group. For subjects missing the follow-up survey, we will impute data from the lower (worse) half of the distribution by the arm (conservative approach). We will also conduct dose analyses, in which we include only those subjects who complete the full intervention. Analyses will use data only for outcomes; (a) increased comprehensive contraceptive knowledge, (b) MHM (c) negotiation and self-efficacy. We will conduct exploratory analyses using outcomes.

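### The secondary covariate-adjusted analysis, as described, can neither sharpen the treatment effect nor correct chance imbalance to any useful degree; adjusting endline for the baseline outcome could do both

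*Protocol article*

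**What the plan says.** All of this stands in the Protocol article, Data analysis plan.

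- **Primary model.** The comparison of binary outcomes "will use mixed-effects longitudinal logistic regression, with random effects for the individual over time".
- **Effect tested.** "Statistically, this amounts to testing for an interaction between time and treatment arm in the longitudinal model".
- **Role of the baseline outcome.** "The baseline will be included as a time point only". It is a response, not a covariate.
- **Arm main effect.** The regression equation includes one: "b_1_ and b_2_ are slopes for the study arm and time, respectively". The baseline difference between arms is therefore estimated freely.
- **Secondary analysis.** The same comparison "adjusting for potentially relevant covariates (e.g., age, education, etc.), in addition to time and treatment arm", with covariates chosen "using backward model selection at the α = 0.15 threshold level". No covariate-by-time term and no adjustment for the baseline outcome is described.
- **Claimed benefit.** "These secondary analyses may improve the precision (power) of estimating the treatment effect and reduce any bias due to random imbalances between arms".

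Missing follow-up is imputed within arm, so every girl contributes two records. The Follow-up survey section places the second survey after the ten-week encouragement period and uses the same questionnaire plus a section on the game.

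**The concern.** In an ordinary endline regression, prognostic covariates remove residual variance and correct for chance imbalance. This model is different. Each girl serves as her own control, so a covariate that is constant within a girl explains only variation that the pairing already removes. A main effect for age or education therefore has almost no route to the time-by-arm interaction.

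Two things are at stake. First, a reader who sees adjusted and unadjusted results agree would take that as reassurance about imbalance, although the agreement is close to a property of the model. Second, the plan holds baseline values of the outcomes and does not use them in the way that would gain precision.

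**Working it through.** The article gives no figure for the expected gain, so there is none to reproduce. The check is algebra plus simulation.

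**1. Linear difference-in-differences.** For girl i with arm s (0/1), time-constant covariate x and girl effect u:

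- baseline: Y1 = a + b1·s + c·x + u + e1
- follow-up: Y2 = a + b1·s + b2 + b3·s + c·x + u + e2
- change: Y2 − Y1 = b2 + b3·s + (e2 − e1)

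Both c·x and u cancel. With two records per girl, the estimate of b3 is the difference in mean change between arms, with or without x. Numerically, adding x changed b3 by less than 1e-14 and left the cluster-robust SE at 0.0268. Only the naive least-squares SE, which ignores the pairing, fell (0.0313 to 0.0292). That apparent gain is spurious.

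**2. Mixed logistic model.** From the article: 1,950 girls, 975 per arm, two waves. Assumed: logit intercept −0.8, time effect 0.4, interaction 0.30, covariate log odds ratio 0.7 to 1.5 per SD, random-intercept SD 0.5 to 1.5, two-sided 0.05. There were 200 data sets per scenario.

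| Scenario | Mean SE ratio, adjusted/unadjusted | Rejection, unadjusted | Rejection, adjusted |
|---|---|---|---|
| log OR 1.0, SD 1.0 | 0.9996 | 0.535 | 0.530 |
| log OR 0.7, SD 1.5 | 0.9999 | 0.485 | 0.485 |
| log OR 1.5, SD 0.5 | 0.9987 | 0.555 | 0.545 |

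The mean absolute change in the estimate was 0.002 to 0.007, against an SE of about 0.155. The two estimates correlated at 0.998 or more. A separate run gave SEs of 0.1540 unadjusted, 0.1539 with the main effect and 0.1541 with covariate-by-time.

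**3. Imbalance.** A covariate imbalance of 0.15 SD was imposed. The SE of a standardised difference here is √(2/975) = 0.045, so this is about 3.3 SEs, deliberately severe. True effect 0.30:

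- Covariate does not predict change: 0.305 unadjusted, 0.305 with the main effect. There is no bias to remove.
- Covariate predicts change: 0.340 unadjusted, 0.340 with the main effect, 0.311 with covariate-by-time. The main effect removes none of the bias.

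**4. Selection at 0.15.** The number of candidates is not given. For k independent noise candidates, the chance of keeping at least one is 1 − 0.85^k: 0.56, 0.73 and 0.80 for k = 5, 8 and 10. The chance that two independent outcomes keep the same noise set is (0.15² + 0.85²)^k = 0.745^k: 0.23, 0.09 and 0.05. Table 4 lists 7 + 8 + 9 = 24 indicators.

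**5. Adjusting endline for the baseline outcome.** On a linear scale, with n per arm, equal variance σ² at both waves and correlation rho:

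- difference-in-differences variance: 4σ²(1 − rho)/n
- baseline-adjusted variance: 2σ²(1 − rho²)/n
- ratio: (1 + rho)/2 = 0.65, 0.75 and 0.85 for rho = 0.3, 0.5 and 0.7

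A simulated risk-difference SE fell from 2.68 to 2.17 points; (2.17/2.68)² = 0.66, in line with rho near 0.3. In the first scenario of step 2, rejection rose from 0.535 to 0.690 with baseline adjustment, and to 0.710 with the covariate added.

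Covariates do real work in this model. With the 0.15 SD imbalance and no effect on change, its log odds ratio was 0.326 without the covariate and 0.261 with it. The latter equals the covariate-adjusted value under balance (0.261).

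**The case against.** The strongest reply is that little is at risk. The analysis is secondary and the sentence says only that it may help. If the covariates cannot move the estimate, it also cannot matter which ones selection keeps. That stands. A reader might infer that selection at 0.15 distorts the effect or its error rate, but no such harm is shown. Nor does the article say that models will differ between outcomes; they can, and with this many indicators probably would.

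A second reply is that a condensed article may omit covariate-by-time terms that a fuller plan contains. The point does rest on reading the covariates as main effects. But the article itself fixes the selection rule, the arm main effect and the claimed benefit, and on that description the benefit does not follow.

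A third reply is that the available gain comes from a different estimator. This is largely right. A reader might quote a single large saving. For example, SEs of 2.63 points for difference-in-differences and 2.07 for the fully adjusted endline model give 1 − (2.07/2.63)² = 38%. That needs an assumed correlation of 0.32 and a strong covariate. Baseline adjustment alone (SE 2.14) supplies 34%, and the covariate then removes only 1 − (2.07/2.14)² = 6% of what remains. With rho unknown, only the range in step 5 can be supported.

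**Conclusion.** The claim of better precision and less imbalance bias does not hold for the analysis described. The result is exact for the linear equation and a very close approximation for the mixed logistic model. It rests on covariates that are constant over ten weeks, main effects only, a free arm main effect and two records per girl. Covariate-by-time terms, baseline-outcome adjustment or a model constrained to equal baseline means would change it; the article describes none of these.

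It would be wrong to infer that the primary analysis is compromised. The unadjusted interaction keeps its validity from randomisation. The consequence is a redundant secondary analysis that could be misread as a robustness check, and an available gain left unused. The point is worth correcting because the correction is nearly free.

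**What to change.** Replace the backward-selected analysis with one pre-specified adjusted model, the same for every outcome. Regress the endline outcome on arm, the baseline value of that outcome, site and a short fixed list such as age and education, and report a standardised risk difference. The unadjusted mixed-model interaction can stay primary.

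If the mixed model is kept for the adjusted analysis, fix the covariate list in advance and add covariate-by-time terms, which address imbalance in predictors of change. Then drop the precision claim, because those terms bring no material gain.

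The cost is analysis-plan wording only; the baseline survey and the site already supply the variables. The drawback is that the secondary estimate is on a marginal scale, different from the primary odds-ratio interaction, so the two should be compared in direction and strength of evidence rather than in size.

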### RCT study

#### Sample size

The study proposes recruiting 1,950 participants from three sites: 650 girls each from Patna, Jaipur, and Delhi NCR for in-person interviews. In addition, 60 girls (n = 20 each from Patna, Jaipur, and Delhi NCR) will be recruited purposively from the encouragement arm of 975 participants for qualitative in-depth interviews. During the encouragement design activity, half of the participants (i.e., 325 girls each from Patna, Jaipur, and Delhi NCR) will receive nudges/encouragement to play the game.

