#### Outcomes measures

The baseline and follow-up survey tools are created with the previously tested tools from standard studies such as the UDAYA study (Understanding the lives of adolescents and young adults) [3], National Family Health Survey (NFHS) [18], Comprehensive National Nutrition Survey (CNNS) [19], Living Standards Measurement Study [20], and other national surveys in India [21]. The primary outcome of the evaluation is to measure improvement in the existing knowledge of MHM, contraception, and increased in agency for adolescent girls making informed decisions and choices in their lives (See Table 4). Several other secondary outcomes measuring intended behaviour change and agency with respect to improvement in decision making, choice of career, negotiation in relationships, and assertion of self-identity will also be evaluated.

**Table 4 Tab4:** List of selected outcome indicators for the study

Outcome indicators	Contents of measurement
Menstrual health management	Percentage of girls who have: - Received any information about MHM - Awareness about sanitary napkins - Awareness about different menstrual hygiene products - Obtained menstrual products alone - Practiced tracking their menstruation with comprehensive understanding of fertility awareness - Experienced trouble in obtaining menstrual hygiene products - Bought menstrual hygiene products online
Contraception	Percentage of girls who have: - Awareness about modern contraceptive methods - Comprehensive knowledge about Oral contraception pills - Comprehensive knowledge about Emergency contraception pills - Comprehensive knowledge about condoms - Comprehensive knowledge about IUD - Comprehensive knowledge about injectables - Practiced refusing sex due to non-availability of contraception - Awareness about condom’s use for prevention of pregnancy and/or infections

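### The worse-half-by-arm imputation in the primary analysis is labelled conservative, but for binary outcomes that is not a general property: it can enlarge the risk difference, and unequal dropout alone creates a false effect

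*Protocol article*

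**What the plan says.** The rule is in the Data analysis plan of the protocol article. The paragraph opens with "The primary analyses will use an intent-to-treat approach and analyze all subjects according to a randomized group". For girls without a follow-up survey it continues: "we will impute data from the lower (worse) half of the distribution by the arm (conservative approach". The rule therefore feeds the primary result and is not a side analysis.

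The outcomes it is applied to are yes/no. The same section states: "The primary comparison of the binary outcomes between intervention groups at baseline and follow-up will use mixed-effects longitudinal logistic regression", with the treatment effect read from the interaction of time and arm. Table 4 (Outcomes measures) introduces its indicators as percentages of girls, for example "Percentage of girls who have".

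The article does not say how a worse half is taken from a yes/no variable or how many imputations are drawn. It does not limit the rule to any range of prevalence or pattern of dropout.

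**The concern.** The label tells readers that any error introduced by the imputation works against finding an effect. That would need the rule to pull the arms together. It draws instead from each arm's own distribution, so an arm that is doing better supplies better imputed values. On a 0/1 scale, half of a distribution is also a crude object: it is all failures when prevalence is 50% or less, and a mixture when it is higher.

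The rule also moves each arm down by an amount proportional to its own dropout. If the arms lose different shares of girls, they separate with no effect of the game. Unequal loss is plausible. The Abstract gives the encouragement arm weekly calls and messages for ten weeks, and under Randomization the controls receive no encouragement. At stake is whether the primary comparison can show an effect produced by the imputation, under a label that says the opposite.

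**Working it through.** **Inputs.** From the documents: 1,950 girls, half encouraged, 3 × 325 = 975 per arm (Sample size); significance at 0.05 (Data analysis plan; two-sided assumed); binary outcomes; the imputation rule. Not in the documents, so assumed: prevalence 20–80%, true effects of 6–7 points, dropout 10–20% and unrelated to the outcome. The article gives no figure for the effect of the rule, so there is none to reproduce.

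**Step 1. The worse half.** Let p be the share with the favourable answer. If p ≤ 0.5, the worse half is all failures. If p > 0.5, it contains p − 0.5 successes out of 0.5, a rate of 2p − 1. So the imputed rate is max(0, 2p − 1), and with dropout m the arm rate becomes

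p′ = (1 − m)p + m·max(0, 2p − 1).

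**Step 2. Equal dropout, true effect.**
- Both arms above 50%: the difference is (1 − m)(p₁ − p₀) + 2m(p₁ − p₀) = (1 + m)(p₁ − p₀). For 76% v 70% and m = 0.2, the rates become 71.2% v 64.0%, so 6 points becomes 7.2. Expected z is 3.41, against 2.68 on the 780 observed per arm.
- Both arms below 50%: the factor is (1 − m), so 6 points becomes 5.4 at 10% dropout and 4.8 at 20%. Here the rule does shrink the effect.
- Arms on either side of 50%: the difference grows if the two rates sum to more than 100%.

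**Step 3. Unequal dropout, no true effect.** Dropout is 10% (encouraged) v 20% (control). The last column is the share of simulated two-proportion endline tests with p < 0.05 (20,000 runs, 975 per arm).

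| True rate, both arms | After imputation | False difference | Falsely significant |
|---|---|---|---|
| 20% | 18% v 16% | 2 points | 21% |
| 30% | 27% v 24% | 3 points | 33% |
| 50% | 45% v 40% | 5 points | 58% |
| 60% | 56% v 52% | 4 points | 43% |
| 70% | 67% v 64% | 3 points | 33% |
| 80% | 78% v 76% | 2 points | 24% |

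Hand check at 30%: z = 0.03/√[(0.27×0.73 + 0.24×0.76)/975] = 0.03/0.0197 = 1.52, and P(Z > 1.96 − 1.52) ≈ 0.33. With 10% v 15% dropout the shares are 19% at a rate of 60%, 17% at 70% and 14% at 80%. Reversing the dropout reverses the sign.

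**Step 4. Equal dropout, no true effect.** The expected difference is zero, but above 50% the imputed values repeat each arm's chance deviation. Take p = 0.7 and m = 0.2, so p′ = 0.64, with one draw treated as observed. The actual standard error is √[1.2² × 0.42/780 + 0.2² × 2 × 0.24/195] = 0.0296. The one reported is √(2 × 0.64 × 0.36/975) = 0.0217. The ratio is 1.36, and a test at 1.96/1.36 = 1.44 rejects about 15% of the time. Simulation also gives 15%. A linear difference-in-differences with within-girl correlation 0.3 gives about 10%.

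**Step 5. The planned mixed model.** The random-intercept logistic model was fitted to expected proportions with 20% dropout in both arms.

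| Random-intercept SD | Baseline; follow-up control v encouraged | Interaction log-odds, true → imputed | Expected z: no dropout / complete pairs / imputed |
|---|---|---|---|
| 1 | 60%; 65% v 72% | 0.387 → 0.409 | 2.63 / 2.35 / 2.91 |
| 1 | 75%; 78% v 84% | 0.451 → 0.458 | 2.68 / 2.39 / 2.87 |
| 2 | 60%; 65% v 72% | 0.523 → 0.505 | 3.04 / 2.72 / 3.22 |
| 2 | 75%; 78% v 84% | 0.596 → 0.554 | 3.06 / 2.73 / 3.16 |
| 1 | 30%; 32% v 39% | 0.367 → 0.319 | 2.45 / 2.19 / 2.10 |
| 2 | 30%; 32% v 39% | 0.498 → 0.405 | 2.85 / 2.55 / 2.37 |

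Above 50%, the estimate rises slightly at SD 1 and falls at SD 2, where imputed values unrelated to a girl's baseline weaken the within-girl correlation. In all four of these cases z exceeds even its value with no dropout. With no true effect and 10% v 20% dropout, the model gives a false odds ratio of 1.15 to 1.27 and a z shift of 0.90 to 1.51. Taking z as normal with unit variance, that is a rejection rate of about 15% to 33%.

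**The case against.** Several points on the other side stand.

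- **The rule can be conservative.** With equal dropout and both arms below 50% it shrinks the effect, and nothing in the document shows where the indicators will lie. A reader might infer that the rule always favours the game. The document does not support that.
- **The factor 1+m is not the bias of the primary estimate.** It is exact for a risk difference. In the planned model's conditional log-odds the enlargement is small and can reverse.
- **The direction of unequal dropout is unknown.** Weekly contact may improve retention, but the section on ethical consideration and consent warns of family backlash over access to this content, which could raise loss among encouraged girls. The bias would then run against the game.
- **The 58% is a worst case.** It needs 50% prevalence and an endline-only test. The range across prevalence and the lower rates for the planned model are the fairer summary.
- **The number of draws is not stated.** The type I error in Step 4 applies only if values are imputed once and counted as observed. Repeated draws would not remove the shift in Step 3.
- **Lost girls may truly do worse.** Part of the downward shift would then be right, and an observed-data analysis would be biased.

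A reader might also infer that the rule runs backwards for "Experienced trouble in obtaining menstrual hygiene products", where a low value is good. The text does not support this, because the bracketed word 'worse' settles the direction whatever the coding.

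Reading the rule as failure for every missing girl does not rescue the label. The enlargement goes, but with no true effect, 70% in both arms and 10% v 20% dropout, the false difference is 0.70 × (0.9 − 0.8) = 7 points.

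Nor is this detail left to an unseen analysis plan: the article itself states the rule and the claim about it.

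**Conclusion.** Wrong as written. Conservatism is not a general property of the rule for binary outcomes. It holds, for the risk difference, when dropout is equal and both arms are below 50%; the plan restricts the rule to neither condition.

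The algebra for the risk difference is exact. The false effects under unequal dropout (2 to 5 points for an assumed 10% v 20%) appear both in the simple comparison and in the planned model, and can go either way. They rest on assumed prevalence and dropout, with dropout unrelated to outcome. The inflated type I error under equal dropout rests further on one imputation counted as data and prevalence above 50%. Two stronger readings are not supported: that the primary log-odds estimate is inflated by 1+m, and that the bias must favour the game.

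**What to change.** Make the primary analysis the mixed-effects logistic model already planned, fitted to all observed baseline and follow-up responses without this imputation. A girl who misses follow-up still contributes her baseline response in her randomised arm. State that the analysis assumes data missing at random, and delete the word 'conservative'.

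Move departures from that assumption to sensitivity analyses: multiple imputation with encouraged-arm dropouts drawn from the control-arm distribution, and a tipping-point analysis with shifts set separately for each arm.

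The cost is a change of wording and a little more analysis, with no new data. The downside is that the primary result then rests on missing at random, which the trial's own data cannot verify. The sensitivity analyses are there to show how far that matters.

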## Abstract

**Background:**

Go Nisha Go™ (GNG), is a mobile game combining behavioural science, human-centric design, game-based learning, and interactive storytelling. The model uses a direct-to-consumer (DTC) approach to deliver information, products, services, interactive learning, and agency-building experiences directly to girls. The game’s five episodes focus on issues of menstrual health management, fertility awareness, consent, contraception, and negotiation for delay of marriage and career. The game’s effectiveness on indicators linked to these issues will be measured using an encouragement design in a randomized controlled trial (RCT).

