**Methods:**

A two-arm RCT will be conducted in three cities in India: Patna, Jaipur, and Delhi-NCR. The first arm is the treatment (encouragement) arm (n = 975) where the participants will be encouraged to download and play the game, and the second arm (n = 975) where the participants will not receive any nudges/encouragement to play the game. They may or may not have access to the game. After the baseline recruitment, participants will be randomly assigned to these two arms across the three locations. Participants of the treatment/encouragement arm will receive continuous support as part of the encouragement design to adopt, install the game from the Google Play Store at no cost, and play all levels on their Android devices. The encouragement activity will continue for ten weeks, during which participants will receive creative messages via weekly phone calls and WhatsApp messages. We will conduct the follow-up survey with all the participants (n = 1950) from the baseline survey after ten weeks of exposure. We will conduct 60 in-depth qualitative interviews (20 at each location) with a sub-sample of the participants from the encouragement arm to augment the quantitative surveys.

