## Baseline and follow-up survey tools

### Quantitative survey

After completing the household listing exercise, the eligible participants will be identified and listed with the help of a screening tool. The final list of respondents will be prepared after de-identifying the individual participants into unique identification respondent IDs. For the main phase RCT study, we will recruit adolescent girls based on the previously mentioned inclusion criteria. The final list will be considered the sampling frame for the recruitment of baseline data collection. Once the sampling frame is developed, the eligible adolescent girls will be approached for data collection of in-person surveys.

The survey tool was prepared and tested in the pretesting of the method. There are eight sections in the baseline questionnaire and nine for the endline. (See Table 3).

**Table 3 Tab3:** Sections in the survey tool

Section	Theme	Description
I A	Household Characteristics	Details of household features, including understanding socio economic level of the household related to household goods/financial condition
I B	Individual Characteristics	Background information on age, siblings, parents, education, livelihood, friends, and career aspirations
II	Media and Technology	Phone and media consumption patterns
III	Health Services Utilization	Availability, accessibility, and preferences for healthcare services
IV	Menstrual Health and Fertility Awareness	SRH information/services received, perception, and attitude towards MHM
V	Empowerment and Aspirations	Understanding of personal aspirations, knowledge/attitudes about career aspirations, preparation for job/career, and financial independence
VI	Negotiation and Consent	Knowledge of attitudes and perceptions towards personal agency, consent in relationships, the legal age of marriage, and consent for sex
VII	Male and Female Relationships	Age-appropriate questions on types of relationships (platonic/physical), attitudes towards dating, perception of acceptable activities in a relationship
VIII	Contraception	Knowledge of methods of contraception, accessibility, and utilization
IX Only for endline survey	Knowledge, Attitude, and Practices: Go Nisha Go	Knowledge of GNG game, levels played, links accessed, product and brand recall, gameplay, and intention for behaviour change and measurement of confidence for negotiation with partner/parents

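### The only exposure-based analysis keeps completers alone, and the stated contrast treats being encouraged as having played; the size of the game's effect therefore gets no valid estimate, although the primary intent-to-treat test stands

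*Protocol article*

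**What the plan says.** The Abstract sets the aim: "The game’s effectiveness on indicators linked to these issues will be measured using an encouragement design in a randomized controlled trial (RCT"). What is randomised is the encouragement: under Sample size, "half of the participants (i.e., 325 girls each from Patna, Jaipur, and Delhi NCR) will receive nudges/encouragement to play the game". The game stays open to the other arm; the Abstract says of those participants, "They may or may not have access to the game".

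The Data analysis plan opens with the contrast: "Analyses will test whether participants who played the game (treatment arm) relative to control participants who have not received any encouragement" to play. Later in the same section the primary analysis is fixed as intent-to-treat, with every subject in her randomised group. The effect is the time-by-arm interaction in a mixed-effects logistic model, and of this unadjusted comparison the article says that the "analysis will provide a causal effect of the intervention". It then adds: "We will also conduct dose analyses, in which we include only those subjects who complete the full intervention". No comparator is given for that analysis, and completing the full intervention is not defined.

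Gameplay will be measured. Section IX of the endline tool (Table 3) covers "Knowledge of GNG game, levels played, links accessed, product and brand recall, gameplay", the follow-up survey goes to all 1,950 girls, and a profile code is meant to link survey records to in-game data.

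**The concern.** In an encouragement trial two questions must be kept apart: what does encouraging girls do, and what does playing do? Randomisation answers the first directly. The opening sentence of the Data analysis plan merges the two by writing playing and treatment arm as one thing, which holds only if every encouraged girl plays. The article gives reason to doubt that: its pretest found that more messages were needed to get girls to download the game and play all five levels.

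The analysis that addresses actual exposure then keeps only completers. Girls who finish are likely to differ from those who do not in motivation, phone access, schooling or family permission. The control arm has no encouragement programme to complete, so no matching group of controls can be picked out. Difference-in-differences removes differences that are constant over time. It does not remove a tendency of finishers to learn or change faster anyway.

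At stake is the figure most likely to be quoted for scale-up, namely how much the game moves knowledge or agency in a girl who plays it. Intent-to-treat will understate that figure where uptake is partial, and the completers analysis can overstate it or create it from nothing.

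**Working it through.** **Figures in the article.** "The study proposes recruiting 1,950 participants from three sites: 650 girls each from Patna, Jaipur, and Delhi NCR for in-person interviews". 3 × 650 = 1,950 = 2 × 975, and 3 × 325 = 975 encouraged. These agree. The article gives no uptake, outcome rate, effect size or power, so everything below rests on assumptions.

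**Assumptions.** Three kinds of girl: always-players (play in either arm), compliers (play only if encouraged) and never-players. Outcome rates without the game: 45%, 35% and 25%. Anyone who plays counts as a completer. Encouragement acts only through play. Completers in the encouraged arm are compared with all controls at follow-up.

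**Formulas.**
- Intent-to-treat difference = effect of playing × (uptake encouraged − uptake control).
- Complier-average estimate = intent-to-treat difference ÷ difference in uptake.
- Completers minus controls with no game effect and no control play = D × (1 − c). D is the difference between would-be completers and the rest in the absence of the game, and c is the share who complete.

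**No game effect.** With 30% compliers and no control play, the control rate is 0.3 × 35 + 0.7 × 25 = 28%. Completers have 35%, so the spurious difference is 7 points, equal to 10 × 0.7. At 50% and 80% it is 10 × 0.5 = 5 and 10 × 0.2 = 2. With 10% always-players and 40% compliers, controls have 4.5 + 14 + 12.5 = 31% and completers (4.5 + 14) ÷ 0.5 = 37%, a difference of 6.

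**True effect of 10 points.** With 30% compliers, completers have 45% against 28%, a difference of 17. The encouraged arm has 0.3 × 45 + 0.7 × 25 = 31%, so intent-to-treat gives 3 and the complier-average estimate is 3 ÷ 0.3 = 10.

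| Always-players / compliers | Completers − controls, no effect | Chance of p < 0.05, no effect | Completers − controls, true 10 | Intent-to-treat, true 10 | Complier-average, true 10 |
|---|---|---|---|---|---|
| 0% / 30% | +7 | 63% | 17 | 3 | 10 |
| 0% / 50% | +5 | 49% | 15 | 5 | 10 |
| 0% / 80% | +2 | 14% | 12 | 8 | 10 |
| 10% / 40% | +6 | 63% | 15 | 4 | 10 |

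Differences are in percentage points. A simulation with 2,000,000 girls per scenario agrees. The chances of p < 0.05 use a normal approximation with 975 controls and 975 × uptake completers. With no game effect, intent-to-treat and the complier-average estimate are both about 0.

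**Difference-in-differences.** The table compares follow-up rates. In a change analysis the same formula holds, with D as the difference in untreated change. If D = 5 points and c = 20%, 40% or 60%, the bias is 5 × 0.8 = 4, 5 × 0.6 = 3 or 5 × 0.4 = 2 points. It vanishes only if finishers and others would have changed equally.

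**Dilution and power.** For a 10-point effect of playing and an assumed 30% control rate, a two-sided 0.05 comparison of proportions with 975 per arm has power of about 30%, 66% and 96% at uptake differences of 30%, 50% and 80%.

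**The case against.** The best defence is that intent-to-treat is primary and the dose analyses come in addition. A reader might infer from the completers sentence that the trial's main effect will come from that subset, or that the trial cannot validly tell whether the game works. The article supports neither. It nowhere makes the dose analyses the headline. If encouragement acts only through play, intent-to-treat is a valid, though diluted, test of no game effect, and a complier-average estimate needs that same assumption. This defence stands.

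A reader might also take the lack of an instrumental-variable analysis as the error. This is a condensed article; the full protocol and SAP are not shown and may contain one. Its absence is not the finding. The completers restriction and the wording of the contrast are written in the article, and an unseen document does not cure them.

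Third, Table 2 names the intervention as the game encouragement design. On that definition the article's phrase about a causal effect of the intervention correctly describes intent-to-treat. That also stands, so only the opening contrast needs correcting.

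Fourth, the dose analysis is under-described: completion might mean all five levels or the ten-week schedule, and the comparator is open. The calculation takes one natural reading. Either meaning is still defined by conduct after randomisation, so the selection problem remains while its size is uncertain.

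Last, ten weeks of calls and messages might themselves change knowledge or confidence. The content of Table 1 is not shown, so exclusion cannot be checked. This limits the proposed estimate and must be stated beside it.

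**Conclusion.** The point holds in a limited form, and its severity is moderate. The randomised comparison is sound as an estimate of the effect of encouragement. Two written elements are not sound: the contrast that equates the treatment arm with girls who played, and an exposure analysis that keeps completers only. The latter gives no valid estimate of the size of the effect of playing. In the scenarios assumed here it shows 2 to 7 points when the game has no effect, and 12 to 17 points when the true effect is 10. These sizes rest on assumed uptake, assumed outcome rates and completers being compared with all controls at follow-up. Under a change analysis they depend on how differently finishers would have changed without the game, which the article does not let anyone determine.

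**What to change.** 1. Keep intent-to-treat as the primary analysis and label its result the effect of encouragement. Reword the opening of the Data analysis plan so that the contrast is between girls assigned to encouragement and girls assigned to none.
2. Replace the completers-only dose analysis with a secondary complier-average estimate on all randomised girls: two-stage least squares on the risk-difference scale, with assignment as instrument. If the completers analysis is kept, define completion and call the result descriptive and non-causal.
3. Make any play the main exposure. Completion of all five levels would be a poor choice, since partial play may also have an effect. Treat number of levels completed as exploratory: with one binary instrument it gives a weighted average per-level effect that is harder to interpret.
4. Ask the gameplay items of Section IX in the same way in both arms, with the profile code as a cross-check, and report uptake by arm.
5. State the exclusion assumption (encouragement works only through play) and monotonicity (no girl plays less because she was encouraged). Note that the calls and messages could themselves affect outcomes.

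The cost is some wording and one further model on data already planned. The standard error is roughly that of intent-to-treat divided by the uptake difference: 1 ÷ 0.3 = 3.3 times as large at a 30-point difference, 2 times at 50 and 1.25 times at 80. The risk difference is also on another scale from the primary logistic model. Instrument strength should not be a problem: at an assumed 40% versus 10% uptake, the first-stage F is 0.30² ÷ [(0.4 × 0.6 + 0.1 × 0.9) ÷ 975] = 266.
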